# Study protocol for daiobotanpito combined with antibiotic therapy for treatment of acute diverticulitis: a study protocol for a randomized controlled trial

**DOI:** 10.1186/s13063-020-04370-7

**Published:** 2020-06-16

**Keywords:** Japanese traditional (Kampo) medicine, Daiobotanpito, Diverticulitis, Da huang mu dan tang, Randomized controlled trial

## Abstract

**Background:**

Colonic diverticular disease has been increasing in prevalence due to the rapidly aging global population, but standard treatment has not changed dramatically in recent years. Daiobotanpito (DBT; *Da Huang Mu Dan Tang* in Chinese) has been used in medical treatment of acute abdominal abscesses, such as appendicitis or diverticulitis in traditional Japanese (Kampo) medicine for many years, based on more than 3000 years of experience. Prior to this study, a retrospective open-label trial was conducted to compare patients with acute diverticulitis who received oral DBT combined with intravenous antibiotics with those who received intravenous antibiotic alone; it showed a positive effect of DBT on acute diverticulitis. We aim to investigate whether moderate to severe acute diverticulitis shows greater improvement with intravenous antibiotics plus orally administered DBT compared with intravenous antibiotics plus placebo.

**Methods:**

This is a two-group, randomized, double-blind, placebo-controlled, multi-center trial, which is designed to evaluate the efficacy and safety of DBT in patients with moderate to severe diverticulitis treated with intravenous antibiotics. Eligible participants will be randomized to either a treatment group receiving a 10-day oral DBT regimen plus conventional therapy or a control group receiving a 10-day placebo regimen plus conventional therapy. The primary outcome will be success in treating diverticulitis: the success rate will be defined as elimination of abdominal pain within 4 days in all patients, and in patients with fever (body temperature ≧ 37.5 °C) on inclusion into this study, fever relief with reduction in body temperature to < 37.5 °C within 3 days. Secondary endpoints will include the number of hospitalization days, changes in inflammatory response (C-reactive protein (CRP), white blood cell (WBC) and neutrophil counts), fever type, number of days before beginning food intake, recurrence rate (observation for 1 year after registration), and adverse event expression rate. Assessments will be performed at baseline and on the day of discharge. The recurrence rate will be recorded at 1 year after registration.

**Discussion:**

This study is expected to provide evidence to support the clinical benefits of DBT in the treatment of acute diverticulitis. It may also provide evidence on the efficacy and safety of DBT in the recurrence of acute diverticulitis.

**Trial registration:**

UMIN-CTR: UMIN000027381. Registered on 27 April 2017.

https://upload.umin.ac.jp/cgi-bin/ctr/ctr_view_reg.cgi?recptno=R000031377, and changed to jRCTs041180063, registered on 30 July 2019; as a result of the revision of the domestic law in 2018 in Japan.

## Background

The prevalence of diverticular disease is estimated to range between 20% and 60% in the general population worldwide [1, 2]. Although 75% of patients with diverticulosis remain symptom-free during their lifetime, the prevalence of patients who require medical or surgical treatment has increased by 16% in the last 20 years, thereby increasing morbidity associated with this condition [3–5]. According to the recommendations from the American Gastroenterological Association on treatment and diagnosis [6] and the Guidelines for Colonic Diverticulitis of the Japan Gastroenterological Association [7], the initial treatment of uncomplicated colonic acute diverticulitis is bowel rest (i.e., fasting) and broad-spectrum antibiotics. Notably, despite the presence of abscess or perforation with colonic diverticulitis, conservative treatment is typically performed for limited peritonitis and abscess. Patients who do not respond to medical therapy should be considered for surgery depending on the clinical situation. Elective resection is recommended after two well-documented attacks, depending on the patient’s age and medical fitness and the severity of the attack.

Moreover, colonic diverticular disease has been increasing in prevalence due to the rapidly aging global population [6]. However, standard treatment has not changed noticeably in recent years.

The unique application of traditional Japanese (Kampo) medicine is gradually attracting worldwide attention. In Kampo medicine, daiobotanpito (DBT; *Da-Huang-Mu-Dan-Tang*) is used for patients with *Yang* (*Yang qi* is a kind of *qi* that mainly has a warming function) - excess in the interior layers of the body, who exhibit signs of local *Qi* (a kind of vital energy) - congestion and blood stagnation. It has traditionally been used to treat abscesses in the intestine, such as in diverticulitis or appendicitis. From the perspective of Kampo medicine, DBT drains heat, dispels blood stasis, disperses clumping, and reduces swelling. It is primarily used in patients with abdominal distention and constipation. DBT consists of five crude drugs: *Rhei rhizoma*, *Natrium sulfuricum*, *Moutan cortex*, *Persicae semen*, and *Benincaseae semen*. Notably, *Rhei radix et Rhizoma* and *Moutan cortex* drain heat and dispel blood stasis. These aspects are attributed to heat and constraints that allow the formation of toxins, which secondarily leads to the formation of pus. The appropriate strategy in Kampo medicine is to discharge the toxin, eliminate the phlegm (the viscous turbid pathological product that can accumulate in the body, causing a variety of diseases), clear the heat, and clear the blockage [8].

As described previously, surgery should be performed in patients who do not respond to medical therapy in difficult or complicated clinical situations. DBT may be an alternative or supportive therapy for patients with acute diverticulitis, which may enable these patients to avoid surgery. Prior to this study, a retrospective open-label trial was conducted to compare patients with acute diverticulitis who received oral DBT combined with intravenous antibiotics with those who received intravenous antibiotics alone; importantly, it showed a positive effect of DBT for treatment of acute diverticulitis. The study included 34 patients: 11 patients in group 1 receiving DBT and 23 patients in group 2 not receiving DBT. There was a significantly improved outcome in the group treated with DBT, compared to the group not treated with DBT, when comparing duration of fever, abdominal pain, and administration of antibiotics [9].

The authors hypothesize that combined treatment with oral DBT is superior to the standard therapy for acute diverticulitis. This study aims to investigate the effectiveness of the treatment of acute colonic diverticulitis with Kampo medicine, DBT.

## Methods/design

### Study design and settings

A brief flowchart of the entire study is shown in Fig. 1. This study is a two-group, randomized, double-blind, placebo-controlled, multicenter trial, which will evaluate the efficacy and safety of DBT in patients with acute diverticulitis. The study will be conducted throughout Japan. Patients will be recruited from the gastroenterology inpatient departments of 13 hospitals. Informed consent will be obtained from all study participants. The study protocol was designed in accordance with the ethical principles in the Declaration of Helsinki and regional regulations. Central ethical approval of this study has been confirmed from the Central Review Board of Kanazawa University Hospital (reference approval number 6058) and we will not begin recruiting at other centers in the trial until local ethical approval has been obtained. This study was registered at https://upload.umin.ac.jp/cgi-bin/ctr/ctr_view_reg.cgi?recptno=R000031377 (UMIN000027381) on 27 April 2017. We had to change our registration from UMIN to https://jrct.niph.go.jp/en-latest-detail/jRCTs041180063 (jRCTs041180063) on 30 July 2019. In Japan, as a result of the revision of the domestic law in 2018, the clinical trial register in accordance with the domestic law has been officially changed for almost all investigator-initiated clinical trials of new investigational drugs. So, we registered the study again with the ethical committee, which was organized according to the new law. After their approval, we changed the registered website from UMIN to jRCT.

**Fig. 1. Fig1:**
[figure not shown]
Study design flow chart

The protocol includes elements recommended in the Standard Protocol Items: Recommendations for Interventional Trials (SPIRIT) [10] checklist (Additional file 1).

### Setting and participants

This study will be conducted in Japan. Patients will be recruited from the gastroenterology and surgery inpatient department at each of the hospitals in different districts in Japan. Participants who meet the following inclusion criteria are eligible:
Moderate to severe diverticulitis: diagnosis will be based on computed tomography (CT) evidence of diverticula-like structure, combined with tenderness or abdominal pain, thickening of the colon wall, signs of inflammation of pericolonic fat, tissue density, and vascular involvement. Pericolonic abscess, free air or extravasation, and accumulation of fluid will also be assessed to predict prognosis.Age at least 20 years and younger than 75 years.Ability to communicate with the investigators.Abdominal pain and/or fever with body temperature > 37.5 °C.Provision of written informed consent for participation after receiving sufficient explanation for participation in this study and achieving sufficient understanding.

Participants who meet the following exclusion criteria will not be enrolled:
Severe organ dysfunction as follows, based on blood tests within 4 the weeks before treatment starts:
Renal function: serum creatinine value 1.5-fold greater than the upper limit of the institutional standard.Liver function: serum aspartate aminotransferase (AST) value or serum alanine aminotransferase (ALT) threefold greater than the upper limit of the institutional standard.Central nervous function: encephalopathy or a patient suspected of having encephalopathy.Electrolytes: serum sodium < 125 mEq/L, serum potassium < 3.3 mEq/L.Highly likely to have abscess perforation due to malnutrition (albumin < 2.5 g/dL).Symptoms of obstructive ileus.Chronic anorexia, abdominal pain, and/or diarrhea symptoms before the onset of colorectal diverticulitis.Performance status (an indicator of general condition and the degree of restriction of the patient’s daily life) ≥ 3 before the onset of colorectal diverticulitis.History of DBT administration.Treatment with insulin preparations.Immunocompromised status.Pregnancy or postpartum status.Advanced allergy to Kampo formulas.

### Randomization, allocation concealment, and blinding

Baseline measures will be obtained before randomization. The web-based online randomization system used in this trial was provided by an independent academic research organization at Kyoto Prefectural University of Medicine. In this registration method, the principal investigator or research coordinator accesses the URL of the Web registration system and registers himself, and obtains the allocation result. For registered case information, the information entered on the case report form (CRF) form is faxed to the data center. Allocation of subjects to each treatment group is performed using the central registration system. In this registration method, researchers access THE Web-based registration and randomization system, and obtain the allocation. Participants are randomized using a minimization method, in which the history of diverticulitis (initial or recurrent) and the severity (with abscess formation on CT and/or C-reactive protein (CRP) ≧ 10 or without abscess formation and CRP < 10) are used as adjustment factor [11]. Enrolled patients who provide informed consent will be randomized 1:1 in a blinded manner into either an experimental treatment group receiving a 10-day DBT regimen plus conventional therapy or a control group receiving a 10-day placebo regimen plus conventional therapy. Only the allocation number is written on the test drug box, and only the data center knows whether the box contains DBT or the placebo. Thus, all participants and treatment providers, those measuring the outcomes, and those who are to analyze the data will be blinded to treatment allocation.

### Interventions

We will use DBT extract, which consists of five crude drugs in fixed proportions: *Rhei rhizoma* (2.0 g), *Natrium sulfuricum* (1.8 g), *Moutan cortex* (4.0 g), *Persicae semen* (4.0 g), and *Benincasae semen* (6.0 g), in 7.5 g of extract. DBT extract (Tsumura, Tokyo) - or placebo manufactured by Tsumura Co., Ltd., based on good manufacturing practice standards - at 2.5 g will be administered three times per day, 7.5 g per day, for 10 days. The placebo does not contain extract of DBT but was made following almost the same process, so that the shape is almost the same as for the DBT. In addition, in order to make the scent and taste closer to the actual drug, some fragrance that does not influence the effect was used. The administration of DBT or placebo begins immediately after informed consent and Web-based randomization. No restrictions will be imposed on the standard treatments for acute diverticulitis or any other disease while DBT is administered. If the clinical evolution is appropriate, a regular diet will be initiated, and the patient will be discharged; the patient will return as an outpatient 1 week later. We will ask all randomized patients whether they have relapsed, 1 year after discharge. When any serious adverse event occurs or patients do not wish to further participate in the trial, they will be excluded from the trial.

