### Primary endpoint

Treatment success rate: If the following criteria are satisfied, treatment will be defined as successful:
In a patient with a fever and body temperature of 37.5 °C and abdominal pain requiring treatment at baseline, both fever relief within 3 days and elimination of abdominal pain within 4 days are confirmed.In a patient with abdominal pain requiring treatment, but who did not have baseline fever and body temperature ≥ 37.5 °C, disappearance of abdominal pain is observed within 4 days.

The definition of symptom change is as follows:
① Fever reliefFever relief is defined as the absence of fever with body temperature ≥ 37.5 °C without the use of antipyretic analgesics. Even when an antipyretic analgesic is used, if the body temperature of 37.5 °C or more does not occur even after 6 h after the administration of the antipyretic analgesic, it is determined that the patient has fever relief.② Elimination of abdominal painElimination of abdominal pain means that there is no abdominal pain without using antipyretic analgesics. Even when the antipyretic analgesic is used, it is determined that the abdominal pain has disappeared if no abdominal pain develops ≥ 6 h after the administration of the antipyretic analgesic. A visual analogue scale (VAS) score for pain should be obtained three times daily during the course of the abdominal pain.

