### Secondary endpoints

The secondary endpoints are:
Number of hospital days: number of days until discharge, including the registration date, after trial registration.Change in inflammatory response (CRP, WBC, neutrophil count): Differences between the value at the time of registration (baseline value) of each measurement and the value at each measurement day.Thermal type: differences between the values at the time of registration (baseline value) of body temperature and the values on each measurement day.Number of days until oral ingestion: number of days until the beginning of oral intake, including the registration date, after trial registration.Recurrence rate (1-year follow-up observation): rate of recurrence at 1 year after randomization. Recurrence after discharge is regarded as diagnosis of colonic diverticulitis.Adverse events (types and frequency of side effects): side effects will be recorded for each observed adverse event, and the type and frequency will be determined.

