### Statistical analysis

The treatment success rate will be compared between groups using the Pearson chi-square test. Time to confirmed treatment-success will be summarized using the Kaplan-Meier method. Continuous variables will be summarized as mean and standard deviation, and comparisons will be made using the unpaired Student’s *t* test. Categorical variables will be summarized as frequency and proportions, and comparisons will be made using the chi-square test. Two-sided *p* values <0.05 will be considered statistically significant.

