### Quality control and trial management

The management structure comprises the principle investigator (PI), a trial management group, and a data monitoring committee. The trial management group is responsible for conducting the trial and will meet monthly to discuss trial progress. The PI will visit each collaborative hospital for face-to-face meetings and sharing of information to promote patient recruitment. The data monitoring committee will review interim safety data and periodically review the conduct of the study. Additionally, all data will be monitored centrally every month. In this study, interim analysis of efficacy is not planned. Final analysis will be performed by the data center and our statistician. Additional monitoring may be performed at the discretion of the monitoring manager. The data monitoring committee has met once prior to the start of patient recruitment. At least twice per year, participating investigators, research assistants, and research nurses will be required to attend a training workshop for clinical research to ensure strict adherence to the study protocol and familiarity with the trial administration process. The data collected in this trial will comprise information recorded in case report forms and questionnaires. Data quality will be checked regularly by research assistants and overseen by monitors; all modifications will be marked on the case report forms, and data managers will recheck the data before they are officially logged. The database will be locked after all data have been cleaned. If participants withdraw from the trial during the study period, the reasons will be documented, and the dropout rate will be statistically analyzed.

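### The rule that takes patients with a serious adverse event out of the trial does not separate stopping drug, follow-up and analysis, and conflicts with 1-year follow-up of all randomised patients

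*Protocol article*

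**What the plan says.** The rule stands in the Interventions section of the protocol article: "When any serious adverse event occurs or patients do not wish to further participate in the trial, they will be excluded from the trial". It applies to patients already randomised, since the same section starts dosing straight after randomisation. The sentence immediately before it reads: "We will ask all randomized patients whether they have relapsed, 1 year after discharge".

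Other sections bear on how such patients are handled:

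- Secondary endpoints, on adverse events: "side effects will be recorded for each observed adverse event". Type and frequency are to be reported.
- Quality control and trial management: "The data monitoring committee will review interim safety data", and for withdrawals, "If participants withdraw from the trial during the study period, the reasons will be documented, and the dropout rate will be statistically analyzed".
- Primary endpoint, for a patient with fever and pain at baseline: success requires that "both fever relief within 3 days and elimination of abdominal pain within 4 days are confirmed". Without baseline fever, only the 4-day pain criterion applies.
- Statistical analysis: "The treatment success rate will be compared between groups using the Pearson chi-square test". No exclusion is set there, and no rule is given for how a patient taken out under the Interventions sentence counts.

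**The concern.** The rule's object is the trial, not the study drug. It puts a serious adverse event on the same footing as the patient's own wish to leave, so a patient who has an event and is willing to stay is still taken out. The trigger occurs after randomisation and may depend on treatment. In moderate to severe diverticulitis, an early serious deterioration will often also be a failure of the day 3/4 endpoint.

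Two things are at stake:

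- **Follow-up.** If it ends at the event, the course of that event, later harms, hospital days and 1-year recurrence are missing for a selected group, possibly of different size in the two arms.
- **Primary analysis.** If the patient is also dropped from it, failures leave the denominator, and the arm that loses more of them looks better.

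**Working it through.** **1. The texts side by side.** One sentence asks every randomised patient about relapse at 1 year. The next takes some randomised patients out of the trial. Both cannot be carried out as written, because a patient who has left the trial cannot also supply the 1-year recurrence outcome. The conflict needs no assumption about analysis sets.

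**2. What each reading of the rule would do.**

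- Stopping study drug only: no follow-up is lost and nothing is biased by the rule. The sentence does not say this.
- Ending participation: the triggering event is still recorded under Secondary endpoints, but later events, hospital days and recurrence are lost.
- Removal from the analysis as well: the success rate is conditioned on not having had a serious event.

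**3. The plan's own figure.** Sample size gives success rates of 75% and 50%, two-sided alpha 5%, power 90%, and 85 per arm (170). The Fleiss formula with continuity correction reproduces 85 per arm. At 85 per arm the uncorrected Pearson test has 92.7% power (normal approximation), and at 83 per arm (2% lost) 92.1%. Power is therefore not the issue; bias is.

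**4. Size of the bias under the third reading.** The documents give no serious adverse event rates, so those below are assumptions. Assume also that every excluded patient is a failure and that true success is 50% in both arms (no effect). With a fraction s excluded from an arm:

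observed success = 0.50 / (1 − s)

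- 10%: 0.50/0.90 = 55.6%. 2%: 0.50/0.98 = 51.0%. Spurious difference 4.5 points.
- 8%: 0.50/0.92 = 54.3%. 3%: 0.50/0.97 = 51.5%. Difference 2.8 points.
- 5%: 0.50/0.95 = 52.6%. 2%: 51.0%. Difference 1.6 points.
- Equal rates: difference zero.

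Rejection rates come from summing the binomial probabilities of all tables in which the two-sided 5% Pearson test rejects, with 85(1 − s) patients per arm rounded down:

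| Excluded (arm A vs arm B) | Patients analysed | Spurious difference | Rejection rate |
|---|---|---|---|
| none | 85 vs 85 | 0 | 5.5% |
| 5% vs 2% | 80 vs 83 | 1.6 points | 5.5% |
| 8% vs 3% | 78 vs 82 | 2.8 points | 6.3% |
| 10% vs 2% | 76 vs 83 | 4.5 points | 9.0% |

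A normal approximation gives 8.8% for the last row, against a nominal 5.0%. In that row, false wins for the arm with more events rise from 2.7% to 8.5%.

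**5. Sensitivity to the all-failure assumption.** If a fraction q of the excluded patients were successes, observed success = (0.50 − q·s)/(1 − s). For 10% versus 2% with q = 25%: (0.50 − 0.025)/0.90 = 52.8% and (0.50 − 0.005)/0.98 = 50.5%, a difference of 2.3 points with 6.1% rejection. With q = 50% the bias is zero.

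**6. At the design rates.** With equal 5% exclusion, all failures, 75% versus 50% is reported as 0.75/0.95 = 78.9% versus 0.50/0.95 = 52.6%. A 25-point difference becomes 26.3 points.

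**The case against.** The strongest reply is that this is a loosely worded withdrawal criterion. It sits in Interventions among conduct items (dosing, diet, discharge, follow-up), not in Statistical analysis, and it groups serious events with patients who no longer wish to take part. The article is condensed, so the full protocol or a statistical analysis plan may define the analysis sets. Their absence here is no fault.

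Much of that stands. A reader might infer that these patients are dropped from the analysis, so that efficacy and safety are both biased. The documents do not support this: no section says they leave the analysis. A reader might also infer that harms are erased. They are not. The triggering event falls under adverse event recording, the data monitoring committee sees interim safety data, and withdrawal reasons are documented. Nor is every serious event a primary failure. The endpoint is settled by day 4, while dosing runs 10 days, so a later event can follow a confirmed success. The larger rates in the table are illustrative; the only attrition figure in the article is a 2% dropout assumption, which is not a serious event rate.

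None of this repairs the sentence. It is a stated rule, not an omission. Nothing shown limits it to stopping study drug, and the conflict with follow-up of all randomised patients remains on any reading that ends participation.

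**Conclusion.** The point holds as a defect of a stated rule. The sentence leaves three different actions undistinguished and contradicts its neighbour. Followed literally, it ends follow-up on an outcome-related event after randomisation, so later harms, hospital days and recurrence are lost selectively.

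Bias in the success rate is conditional, not established. It requires that these patients also leave the primary analysis, that the event rates differ between arms, and that the excluded patients succeed less often than the rest. Under the all-failure assumption it ranges from 1.6 points with no material inflation (5% versus 2%) to 4.5 points and about 9.0% rejection (10% versus 2%), in favour of the arm with more serious events. At equal rates there is no false difference when treatment has no effect. The correction is worth making because it is cheap and protects the randomised comparison whatever the event rates prove to be.

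**What to change.** Reword the sentence in Interventions and reconcile it with the 1-year follow-up, so that it says:

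- A patient who has a serious adverse event, or who stops study drug, remains in follow-up unless consent to follow-up is withdrawn.
- That patient is analysed in the assigned arm.
- For the primary endpoint, success confirmed in the day 3/4 window counts as success, including when a serious event comes later. Otherwise the patient counts as not successful.

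Any rule on stopping study drug is left as it is; the change concerns follow-up and analysis only.

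The cost is a wording change and a little more follow-up. The primary endpoint window is only 4 days and these are inpatients, so most of the added assessment falls in the same hospital stay. Reported success rates may be slightly less favourable. The sample size of 170 need not change.
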